### Trial management and quality control

A data monitoring committee (DMC) has been established to store, monitor, and check the authenticity, security, and integrity of the database. All members in the DMC are independent of the study sponsors and declared no competing interests. The DMC will periodically review the accumulated data and communicate the problems of its deliberations to the study team if necessary. The frequency of the interim analyses will be judged by the Chair of the DMC, based on the consultation with the sponsor and principal investigator. We anticipate that there might be 2–3 interim analyses before the final analysis.

Data from the paper surveys will be manually entered into an electronic, password-protected database by trained data entry staff. In case of data discrepancies, data quality inspectors will request data clarification from the researchers, and refer to original files and rules to remove outliers. The CRF was promptly sent to the data statistician in our institution. The data manager should check the data again before data analyses. If there is any problem, the data manager should check the original records, and contact with the researchers. Another trained staff will review and inspect > 20% of all entered survey data to ensure accuracy. The aforementioned original data will be stored on password-protected computers as a backup. All electronic data will be stored on a public platform at http://www.medresman.org, which is sponsored by the China Clinical Trial Registry. The database uses standard techniques to provide security. Access to the database is controlled by user names (principal investigator) and encrypted passwords.

A semi-annual audit will be conducted to protect the integrity of all collected data as part of this trial. The principal investigator will ensure that data collection is conducted and reported according to the protocol. There will be semi-annual auditing trials to ensure the protocol is followed, there are no issues with the informed consent procedure, and record keeping is accurate.

### Confidentiality

All participants enrolled in current trial will be firstly assigned a random number (detailed in the “Randomization and allocation” and “Blinding” part), by which all information collected from participants will be documented. This random number will be the only identifier for participants and there will be no other information that would reveal the participants’ identity. Participants will never be identified by name on consent forms. A list of participants with corresponding identifying random numbers will be made and preserved only by the principal investigator, and this list will be kept on a password-protected computer system, separate from all other data files.

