### Randomization and allocation

The total sample size is 68, and these participants will be randomly divided into two groups, 34 each. Eligible patients will be marked by random numbers. We carry out a randomization process using SPSS 12: first, set the random seed and record, generate random numbers for each participant, and then sort the random numbers in ascending order. The first 34 are the first group (UM group), and the last 34 are the second group (MTRS group). The concealed randomization sequence file will be constructed and kept in sequentially numbered, sealed, opaque envelopes by a staff member in the Eye and ENT Hospital of Fudan University outside the study team. When a patient is officially enrolled, the staff member will be called by telephone and open the corresponding envelope to find the randomized treatment for this patient. Assessors in examination rooms and statistician analysts are not allowed to receive information of the group allocation.

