### Blinding

This study is double-blinded. Investigators, eligible patients, and data analysts are all blinded to the group allocations during the trial: investigators do not know which group the patients are assigned; patients do not know which treatment strategy they are given; analysts do not know which group they analyze.

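### The participant identifier is, as written, the random number whose rank fixes the arm, so anyone holding the full list of identifiers can recover the allocation

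*Protocol article*

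**What the plan says.** Randomization and allocation (protocol article) begins the process with "Eligible patients will be marked by random numbers". The SPSS step is then to "generate random numbers for each participant, and then sort the random numbers in ascending order", and the rule that turns rank into arm is "The first 34 are the first group (UM group), and the last 34 are the second group (MTRS group"). The sequence file goes into sequentially numbered, sealed, opaque envelopes held by a staff member outside the study team, who opens the matching one when a patient is officially enrolled. Assessors and analysts may not receive allocation information.

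Confidentiality says that each enrolled participant "will be firstly assigned a random number (detailed in the “Randomization and allocation” and “Blinding” part"), that all collected information is filed under this number, and that "This random number will be the only identifier for participants". The principal investigator keeps the list linking participants to their numbers.

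Blinding states that investigators, patients and analysts are all blinded, and for the last of these that "analysts do not know which group they analyze".

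**The concern.** A study identifier should carry no information about the arm. Here the only random number that the article describes is the one that is sorted to form the groups, and the Confidentiality section makes a random number, by reference to that description, the label on every record. The label then orders participants by arm: all UM identifiers lie below all MTRS identifiers. The published rule also says which half is which.

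Several decisions on records filed under these identifiers involve judgement: recording withdrawals and their reasons, including low listening time (Withdrawal/retention of participants); resolving discrepancies and removing outliers (Trial management and quality control); and the per-protocol analysis (Data analysis). Staff who can infer the arm could, even without intent, treat such cases differently by arm. The research team developed and patented MTRS and expects it to be superior, so the blinding has to be credible.

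**Working it through.** The article states no figure on this point to reproduce. The check is to set the sections side by side and then ask how much an identifier reveals.

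**1. Is the identifier the sort key?** Confidentiality points to two sections for the number. Blinding mentions no number. Randomization and allocation mentions one random number per participant, the one that is sorted. No separate study identifier appears anywhere. On the text, the identifier is the sort key. If it were instead the position after sorting, identifiers 1 to 34 would be UM and 35 to 68 MTRS, which is more transparent still. Only a number unrelated to the sort, such as enrolment order, would be harmless, and the article does not say that one is used.

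**2. Holder of the full list.** Inputs: "The total sample size is 68, and these participants will be randomly divided into two groups, 34 each", and the rank rule. Sort the 68 identifiers and cut after the 34th: 34 + 34 = 68, all arms recovered. This uses ranks only and needs no assumption about how the numbers are distributed.

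**3. Holder of one identifier, range known.** Assume numbers uniform over a known range (the article gives neither the distribution nor the range) and guess MTRS above the midpoint. Let X ~ Bin(68, 0.5) be the count below the midpoint. The number guessed wrongly is |X − 34|. Expected share wrong:

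E|X − 34| / 68 = 34 × C(68,34) / 2^68 / 68 ≈ 34 × 0.0964 / 68 ≈ 0.048

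That is about 95.2% correct; a simulation of 100,000 allocations gave 0.9517. Errors cluster near the cut. For identifiers in the lower or upper 40% of the range (about 80% of them), the simulated guess was right about 99.7% of the time.

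**4. Holder of a subset, range unknown.** Split k randomly chosen identifiers at their own median. Let H be the number of UM participants among them, hypergeometric (68, 34, k). Expected accuracy is 1 − E|H − k/2| / k, which again depends only on ranks. For k = 4, C(68,4) = 814,385:

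- P(H = 1) = P(H = 3) = 34 × 5,984 / 814,385 = 0.250
- P(H = 0) = P(H = 4) = 46,376 / 814,385 = 0.057
- E|H − 2| = 2 × 0.250 × 1 + 2 × 0.057 × 2 = 0.728
- accuracy = 1 − 0.728 / 4 = 0.82

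Simulated values (4,000 draws for each k):

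| Identifiers seen | Arms guessed correctly |
|---|---|
| 4 | 82% |
| 10 | 89% |
| 20 | 93% |
| 34 | 95% |
| 48 | 97% |
| 68 | 100% |

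An identifier generated independently of the randomization key would predict the arm at chance, 50%.

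**The case against.** The strongest reply is that the identity of the two numbers is inferred. The sequentially numbered envelopes imply that a second number links patient to envelope, and the cross-reference in Confidentiality is loose, since Blinding describes no number. The phrase about the only identifier serves privacy and may not have been meant to specify the identifier's format. The article is condensed, and a full protocol may describe a neutral identifier. Part of this stands: practice may differ from the text. But the article does not merely omit the identifier's format. It fixes the identifier by reference to a section where the only random number is the sort key. The envelopes protect the sequence file; they do not protect a label on every record whose rank is the allocation.

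Four stronger readings that a reader might infer are not supported:

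- *Anyone who sees one identifier knows the arm.* That person also needs the rule and either the number range or other identifiers, and an identifier near the cut stays uncertain.
- *Allocation concealment is lost.* Randomization and allocation speaks of marking eligible patients, Confidentiality of enrolled ones, and neither gives the timing relative to enrolment. The sequence is held outside the team.
- *Patient blinding is broken.* Nothing suggests that patients see other participants' identifiers.
- *Otologists discuss Tinnitus Handicap Inventory scores in counselling.* The counselling content listed under Procedure does not include this; the scale is self-reported.

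**Conclusion.** The point holds for those who hold the identifiers in bulk. As written, the rank of the identifier is the allocation, which contradicts the blinding of investigators and analysts stated in Blinding and the withholding of allocation from assessors and analysts stated in Randomization and allocation. The 100% recovery from a full list rests on one premise, that the number in Confidentiality is the one sorted in Randomization and allocation. The 95% figure for a single identifier rests additionally on uniform numbers over a known range. The subset figures need no range but assume a random subset. The effect on concealment is a risk that depends on when numbers are attached, not an established failure. The size of any resulting bias in the outcome cannot be derived from the article.

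**What to change.** Amend two sections of the protocol.

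- Confidentiality: state that the study identifier is assigned independently of the randomization key, for example by order of enrolment, and remove the cross-reference that equates it with the randomization number.
- Randomization and allocation: state that the random numbers and the arm key stay with the staff member outside the study team, and that analysts receive only a coded arm label until database lock.

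If identifiers have already been issued from the sort key, the same staff member should replace them with neutral ones in the files that investigators, assessors and analysts use.

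The cost is a few sentences and, at most, one re-keying of identifiers. No extra patients or staff are needed. A different randomization method, such as permuted blocks, would not by itself close this leak and is not required for it.

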## Discussion

The pathogenesis of tinnitus remains unclear, which is probably related to abnormal variations on the auditory pathway [8]. Tinnitus frequency is often corresponding to the hearing impairment region inside the cochlea [2], thus we invented a strategy to modulate the peaceful music and jointly enhance the upper and lower frequency band adjacent to tinnitus pitch based on the lateral inhibiting effect [27, 28], and the modified sound could be generated and played via our patented software/APP named Fudan Tinnitus Relieving System (FTRS). We plan to verify and compare the clinal efficacy of MTRS to UM in the current RCT. Unmodulated white noise, instrumental music, and natural sounds are often used as controls in clinical trials and they have been generally proven to be less effective than those modified sounds in tinnitus relief [29–31]. Thus, we rationally speculate that MTRS would be effective in reducing negative impacts caused by subjective tinnitus and represent a meaningful advancement in tinnitus intervention.

Anxiety and depression are the common negative emotions concomitant with tinnitus, which in turn aggravate tinnitus suffering, thus forming a vicious cycle [5]. Tinnitus may be transient, intermittent, or persistent in a life-long time, thus education counseling including information support, is crucial for all patients in every phase during a systematic and comprehensive treatment. CBT converts the false and passive perception of tinnitus, reconstructs the positive cognition related to tinnitus, and alleviates the psychological discomforts through various methods, such as relaxation training, mindfulness-based training, and meditation [1]. CBT can observably improve the patients’ quality of life, and alleviate their anxiety and depression [26, 32, 33]. We designed the otologist-leading CBT for tinnitus, that is, figuring out the pathogenesis of tinnitus according to the inspection results and medical history, discussing the possible detriments induced by tinnitus with patients, and providing treatment methods, along with conducting the psychological counseling and behavior training. In this current trial, we plan to integrate customized acoustic therapy with CBT, anticipating to simultaneously mitigate tinnitus suffering and reduce the psychological discomforts (e.g., insomnia, anxiety, and depression) deriving from tinnitus.

A few potential issues related to current RCT should be addressed carefully. This trial has a time-consuming follow-up period, totally having 5 timepoints (when participants are allocated and 1, 3, 9, and 12 months after commencing treatment) for investigators to collect trial data, as a result, there unavoidably will be some participants withdraw from our trial due to different reasons. To reduce the follow-up loss to the maximum, we keep in touch with all participants and timely resolve their encountered problems through multiple ways, such as phone calls, WeChat, and email. Moreover, data input of the assessment scales should avoid manual input errors, by which the electronically input/recording and online submitting will be preferentially adopted, and recorded data will be gathered and exported into statistical analysis software in the background. Also, one assigned investigator will examine the imported data that coming from the CRF (case report form) paper table and dispose of the relevant mistakes or omissions in time.

In conclusion, our trial will concretely and detailly provide the clinical evidence for acoustic therapy by the randomized controlled comparisons between our patented MTRS and UM. Based on preliminary observation and clinical experiences, we hypothesize that the effects of MTRS will be superior to those of UM in terms of the aforementioned outcome measurements and assessment scales. Specifically, we expect that participants in the MTRS group will experience more significantly reduced THI scores, lessened AIS and VAS scores, and better subjective tinnitus relief.

### Study status and recruitment

The planned date of the first enrolment is 15 March 2021. The estimated time required for recruitment is 9 months. The total duration of this study is expected to be 24 months, including statistical analysis, research paper writing, and submitting. This protocol version number is Ver.2.

### Ethics and disseminations

This protocol and the template informed consent forms have been reviewed and approved by the institutional review board (IRB) and the Ethical Committee of Eye & ENT Hospital of Fudan University (Reference Number: 2017047). The research team will make safety and progress reports to the IRB at least annually and within 3 months of study completion. Patients and the public are not involved in the design of this study. The study results will be informed to the public via peer-reviewed journals or academic conferences. The full protocol and dataset will be available from the corresponding author upon reasonable request.
